# Improving Airways Patency and Ventilation Through Optimal Positive Pressure Identified by Noninvasive Mechanical Ventilation Titration in Mounier-Kuhn Syndrome: Protocol for an Interventional, Open-Label, Single-Arm Clinical Trial

**DOI:** 10.2196/14786

**Published:** 2020-08-14

**Keywords:** Mounier-Kuhn syndrome, trancheobronchomegaly, tracheobronchomalacia, positive pressure, bronchoscopy

## Abstract

**Background:**

Mounier-Kuhn syndrome or congenital tracheobronchomegaly is a rare disease characterized by dilation of the trachea and the main bronchi within the thoracic cavity. The predominant signs and symptoms of the disease include coughing, purulent and abundant expectoration, dyspnea, snoring, wheezing, and recurrent respiratory infection. Symptoms of the disease in some patients are believed to be pathological manifestations arising due to resident tracheobronchomalacia. Although treatment options used for the management of this disease include inhaled bronchodilators, corticosteroids, and hypertonic solution, there is no consensus on the treatment. The use of continuous positive airway pressure (CPAP) has been reported as a potential therapeutic option for tracheobronchomalacia, but no prospective studies have demonstrated its efficacy in this condition.

**Objective:**

The purpose of this is to identify the presence of tracheobronchomalacia and an optimal CPAP pressure that reduces the tracheobronchial collapse in patients with Mounier-Kuhn syndrome and to analyze the repercussion in pulmonary ventilation. In parallel, we aim to evaluate the prevalence of obstructive sleep apnea/hypopnea syndrome.

**Methods:**

This interventional, open-label, single-arm clinical trial will enroll patients who are diagnosed Mounier-Kuhn syndrome. Patient evaluation will be conducted in an outpatient clinic and involve 3 visits. Visit 1 will involve the collection and registration of social demographic, clinical, and functional data. Visit 2 will entail polysomnography, bronchoscopy for the evaluation of tracheobronchomalacia, titration of the optimal pressure that reduces the degree of collapse of the airway, and electrical impedance tomography. In visit 3, patients exhibiting a reduction in collapse areas will be requested to undergo chest computed tomography during inspiration and forced expiration with and without positive pressure (titrated to determine optimal CPAP pressure).

**Results:**

This protocol is a doctorate project. The project was submitted to the institutional review board on January 24, 2017, and approval was granted on February 2, 2017 (Brazilian Research database number CAAE 64001317.4.000.0068). Patient evaluations started in April 2018. Planned recruitment is based on volunteers’ availability and clinical stability, and interventions will be conducted at least once a month to finish the project at the end of 2020. A preliminary analysis of each case will be performed after each intervention, but detailed results are expected to be reported in the first quarter of 2021.

**Conclusions:**

There is no consensus on the best treatment options for managing Mounier-Kuhn syndrome. The use of positive pressure could maintain patency of the collapsed airways, functioning as a “pneumatic stent” to reduce the degree of airflow obstruction. This, in turn, could promote mobilization of thoracic secretion and improve pulmonary ventilation.

**Trial Registration:**

ClinicalTrails.gov NCT03101059; https://clinicaltrials.gov/ct2/show/NCT03101059.

**International Registered Report Identifier (IRRID):**

DERR1-10.2196/14786

## Introduction

Mounier-Kuhn syndrome (MKS) or congenital tracheobronchomegaly is a chronic and rare airway morbidity associated with recurrent respiratory infections and characterized by dilation of the trachea and the main bronchi [1]. This disease was first clinically described by Mounier-Kuhn in 1932 [2]. The estimated prevalence of this syndrome in patients with pulmonary symptoms is between 0.4% and 1.6%, and it mostly affects the male gender [1,3-5]. Diagnosis of the MKS is frequently made in the third or fourth decade of life when the symptoms are more exuberant [6]. Histological alterations seen in the disease can be used to explain structural defects such as tracheobronchomalacia (TBM), saccular diverticula between cartilages, and bulging and dilation of the trachea and bronchi [1,7].

The predominant signs and symptoms of the disease include coughing, purulent and abundant expectoration, digital clubbing, dyspnea, snoring, wheezing, and recurrent respiratory infection [1]. The disease could be associated with other comorbidities such as gastroesophageal reflux disease, chronic obstructive pulmonary disease, bronchiectasis, and obstructive sleep apnea/hypopnea syndrome (OSAHS) [1,8-12].

Some of the observed symptoms could be a consequence of TBM occurrence in some patients, which is defined by more than 50% collapse of the intrathoracic trachea and bronchi [13-16]. The main clinical consequences of TBM are obstruction to expiratory airflow; secondary air trapping; decrease in the effectiveness of cough and bronchial hygiene; and facilitation of conditions that promote microorganism colonization, leading to recurrent respiratory infection [4,13].

Despite the patient’s normal pulmonary function, the occurrence of obstructive ventilatory disorder is not uncommon [1,17-19]. Thorax computed tomography (CT) shows dilatation of the trachea and the right and left main bronchi [4,20,21]. Tracheobronchial diverticula, bronchiectasis, air trapping, and emphysema are common findings, suggesting involvement of the small airways [1,7,10,11,22-26]. Bronchoscopy is the gold standard examination for TBM diagnosis [12,14-16,26].

Since TBM is a rare and poorly studied disease, there is no consensus on a specific therapy. Therapeutic management includes inhaled bronchodilators, corticosteroids, hypertonic solution, and mucolytic agents. Some complementary tools used for disease management include noninvasive positive respiratory pressure, vaccination, respiratory physiotherapy, and pulmonary rehabilitation [1,27-29]. Continuous positive airways pressure (CPAP) support has been reported as an option for the treatment of tracheomalacia [5,15,30]. The rationale for using positive pressure in TBM is to recover the patency of the collapsed airways, thereby reducing airflow obstruction and promoting sputum clearance.

Previous experience has shown that CPAP can reduce symptoms, infections, and morbidity/mortality caused by TBM [5,15,31-33]. Additionally, it is an effective therapy in patients diagnosed with concomitant OSAHS [34-36]. This study has two main objectives. First, we aim to confirm the presence of tracheal collapse and the main bronchi of patients with MKS through respiratory endoscopy. Second, we will attempt to optimize the pressure with the CPAP approach to reduce or reverse the pathological consequences of the syndrome on the ventilatory pattern. We also will investigate the prevalence of OSAHS in this population. We hypothesize that maintenance of greater patency of airways could improve pulmonary ventilation for a longer time, reduce symptoms, and improve the quality of life of these patients.

## Methods

### Overview

This is an interventional, open-label, single-arm clinical trial to be conducted on patients diagnosed with MKS, who are followed up in the outpatient clinic from a tertiary university hospital. Eligible patients diagnosed with MKS who are followed up and agree to participate in the study will be requested to sign an informed consent form after verbal explanation and clarification of the study are provided by the investigator.

The following patients will be excluded from the study: those who are contraindicated for bronchoscopy (with thrombocytopenia, incorrigible coagulopathies, refractory hypoxemia, recent acute myocardial infarction, unstable angina, acute cardiac arrhythmias, and refractory bronchospasm), pregnant women under the age of 18 years, and those suspected of having or diagnosed with mycobacteriosis or other related risk factors by the clinical investigator. The study is approved by the institution's ethical review board and funded by the Division of Pulmonology Obstruction Group.

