### Study Design

The study will be conducted in three steps including three patient visits. During visit 1 (day 1), sociodemographic information, modified Medical Research Council dyspnea questionnaire measures [37-39], the Saint Georges Respiratory questionnaire measures [40,41] for health-related quality of life, and most recent spirometry values will be recorded. In addition, all eligible patients will receive 40 mg/day oral prednisone for 7 days before endoscopy, to reduce pulmonary secretion and possible airways hyperreactivity. If the patient presents signs or symptoms that characterize an acute pulmonary infection, the inclusion will be postponed, and specific treatment will be prescribed to reschedule the inclusion.

During visit 2 (day 7 ± 3 days from visit 1), polysomnography and respiratory endoscopy will be performed. Full-night polysomnography will be performed in accordance with the recommendations of the American Academy of Sleep Medicine [42,43].

After polysomnography, a strap of 32 self-adhesive electrodes strap will be attached at the level of fourth intercostal space around the chest, and patients’ electrical impedance tomography data will be recorded concomitantly with bronchoscopy. Bronchoscopy will be performed in two stages: (1) sedation, analgesia, and evaluation of the presence of TBM followed by bronchial hygiene and (2) optimal pressure titrations to decrease airway collapse and EIT performance. The procedure sequence will be conducted in two stages, as described below.

#### Stage 1

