**Figure 1 figure1:**
[figure not shown]
Bronchoscopic view of the trachea and the catheter (blue). Trachea during 0 cm H2O pressure during inspiration (A) and during expiration (B). Trachea in 18 cm H_2_O pressure during inspiration (C) and expiration (D)

 Through observational analysis and after a complete consensus among the bronchoscopists is reached, the minor pressure capable of reducing the degree of collapse in the trachea will be defined (P1). This procedure will be repeated in the main bronchus presenting major collapse. The entire procedure will be documented through video recording, and the images will be analyzed with software assistance (Image Processing Toolbox, Matlab). Measures in the airway variation area will be analyzed by comparing the area of collapse at 0 cm H2O pressure with the corresponding measurements at different applied pressures titrated during the procedure. This analysis will allow us to find the pressure that reduces the degree of airway collapse (P2) [42,43]. EIT will be used for impact analysis of different pressures on pulmonary ventilation (distal airways), a functional imaging method that uses low-intensity electric currents. EIT can dynamically evaluate regional pulmonary ventilation by analyzing impedance variations and minimum impedance in a given thoracic segment by reproducing them in two-dimensional images. It is a noninvasive method that does not use ionizing radiation [44-47].

The EIT data will be acquired using ENLIGHT (Timpel), which produces 50 images per second, sampled in real time [44-47]. Distribution of ventilation will be analyzed at each CPAP level during the positive and expiratory pressure (PEEP) titration maneuver by dividing the EIT image into 4 quadrants (regions of interest, ROI), 2 of which will be gravity dependent (lower lobes) and 2 will be gravity independent (upper lobes). In patients who present tracheomalacia during bronchoscopy, a chest CT will be performed at visit 3 during inspiration and forced expiration in the presence or absence of CPAP. The ideal pressure for this will be obtained during bronchoscopy with an aim to evaluate and document the reduction of tracheal collapse. The images will be obtained by multislice tomography. No intravenous contrast will be administrated.

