### Statistical Analysis

Because MKS is a rare disease, there will be no sample size calculation. It will be a convenience sample including all eligible patients from Mounier-Kuhn reference centers in Brazil. As of July 2020, we are following at least 15 patients with MKS.

We will perform five main types of descriptive analysis on the data: (1) sociodemographic data of all MKS populations included in the study; (2) comparative analysis of the clinical-functional data of patients with and without collapse; (3) prevalence of sleep apnea/hypopnea syndrome; (4) repeated measurement techniques (bidirectional analysis of variance and Tukey or Sidak post hoc test when there is a difference) correlating the pressure that reverses the collapse (P1 and P2), to analyze the difference between airway collapse that occurs with and without PEEP; and (5) comparisons in the distribution of EIT ventilation with and without PEEP. Statistical analysis will be performed with statistical packages Sigma Stat V3 or SPSS V22, and an α level ≤.05 will be considered significant for all tests.

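### The exclusion covering pregnancy and age is worded as one item, so as written it removes only pregnant minors and leaves pregnant adults and non-pregnant minors eligible

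*Protocol article*

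**What the plan says.** The Overview in the Methods of the Protocol article gives the exclusions in one sentence with three items:

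- contraindication to bronchoscopy, spelled out as "thrombocytopenia, incorrigible coagulopathies, refractory hypoxemia, recent acute myocardial infarction, unstable angina, acute cardiac arrhythmias, and refractory bronchospasm";
- "pregnant women under the age of 18 years";
- "those suspected of having or diagnosed with mycobacteriosis or other related risk factors by the clinical investigator".

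On the inclusion side, the Overview describes a trial "conducted on patients diagnosed with MKS, who are followed up in the outpatient clinic from a tertiary university hospital", with signed consent. The Abstract says only that the trial "will enroll patients who are diagnosed Mounier-Kuhn syndrome". The Statistical Analysis section adds: "It will be a convenience sample including all eligible patients from Mounier-Kuhn reference centers in Brazil".

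Under Study Design, "all eligible patients will receive 40 mg/day oral prednisone for 7 days before endoscopy". Stage 1 describes intravenous sedation for the bronchoscopy. Stage 2 says that, for patients found to have tracheomalacia, "a chest CT will be performed at visit 3 during inspiration and forced expiration in the presence or absence of CPAP".

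**The concern.** The middle exclusion is a single noun phrase. No comma, 'and' or 'or' separates pregnancy from age, so the age limit qualifies the pregnant women and does not stand as a criterion of its own. Nothing in the article explains why a pregnant minor should be kept out while a pregnant adult is admitted, or why minors should be excluded only when pregnant.

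The first thing at stake is patient protection. Pregnancy and minority are being screened in a study that gives a systemic corticosteroid, intravenous sedation, an invasive procedure and, for some, ionizing radiation. The second is the definition of the population. With no working age limit, the article does not say whether its descriptive results, including the prevalence of sleep apnea, refer to adults only. Because the sample is to contain all eligible patients, the eligibility text alone decides who enters.

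**Working it through.** No calculation in the plan bears on this point. The check is a logical reading of the criterion, followed by a search of the article for any other rule that would close the gap.

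**Step 1. Literal effect of the item.** It excludes a person only if pregnant AND under 18.

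| | Under 18 | 18 or over |
|---|---|---|
| Pregnant | excluded | not excluded |
| Not pregnant | not excluded | not excluded |

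If pregnancy and age were two separate exclusions, the rule would be pregnant OR under 18, and three cells would be excluded. The two readings differ in exactly two cells: pregnant adults and non-pregnant minors.

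**Step 2. Does another rule cover those two cells?**

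- Inclusion (Abstract and Overview): defined by diagnosis, clinic follow-up and consent. No age limit and no pregnancy condition.
- Listed bronchoscopy contraindications: neither pregnancy nor age appears.
- Investigator-judgement item: attached to mycobacteriosis and related risk factors. It names neither pregnancy nor age.
- Study Design and Statistical Analysis: no further eligibility condition on either.

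No text closes either cell.

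**Step 3. What do patients in those cells face?**

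- Prednisone before endoscopy: all eligible patients (Study Design).
- Sedated bronchoscopy: all eligible patients (Stage 1).
- Chest CT: conditional. Stage 2 gives it to patients with tracheomalacia at bronchoscopy, while the Abstract gives it to those whose collapse is reduced. For a patient who meets the condition, 2 breathing phases × 2 CPAP conditions = up to 4 acquisitions. This assumes one acquisition per combination and takes the Abstract's reading that imaging is done both with and without CPAP.

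**Step 4. How many patients?** The article does not say. The Statistical Analysis section mentions at least 15 patients under follow-up as of July 2020, with no breakdown by age, sex or pregnancy. No proportion can be derived.

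**The case against.** The strongest reply is that this is a drafting slip in a condensed journal article. An exclusion limited to pregnant minors is so implausible that any investigator would read it as two criteria. The operating rule is in the ethics-approved protocol, which may be worded correctly. Patients are known to the clinic and sign consent themselves, with no mention of a guardian, which fits an adult study. The Introduction says that the disease mostly affects males and is often diagnosed in the third or fourth decade of life, so few minors or pregnant women would be expected.

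Much of this stands. A slip is the likeliest explanation, the approved protocol cannot be judged from the article, and the number affected may be small. It does not make the sentence sound. This is not a detail left to a fuller document: the article states a rule on pregnancy and age, and states it in a form that does not work. The consent wording is not an age limit. Being mostly male still leaves women, and the third and fourth decades (ages 20 to 39) are child-bearing years. The Statistical Analysis section also refers to several reference centers, so a shared understanding within one clinic is not enough to rely on.

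A reader might infer three stronger things, none of which the article supports. One is that pregnant patients or minors have been enrolled, or that they make up some given share of the sample; the article reports no such patient. Another is that everyone admitted through the gap would have CT; CT depends on the bronchoscopy findings. The third is that the authors chose this rule; a merged pair of criteria is the more natural explanation.

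**Conclusion.** The exclusion is wrong as written. Taken literally, it leaves pregnant adults and non-pregnant minors eligible for prednisone and sedated bronchoscopy and, if they meet the condition on bronchoscopy findings, for chest CT. This follows from the wording alone and needs no assumption.

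That two criteria were merged by mistake is a strong inference, to be settled against the ethics-approved protocol. The size of the effect is unknown: it may be no patients at all, and no percentage of the sample can be defended. No estimate or test is shown to change. The point deserves correction because the rule is operative and safety-related, evaluations had already begun when it was published, and the correction is very cheap.

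**What to change.** 1. Compare the sentence in the Overview with the eligibility criteria in the ethics-approved protocol.
2. If the approved protocol has pregnancy and age as separate exclusions, list them as two items in the article. If the approved text carries the same merged wording, have the sponsor state the intended criteria and amend the protocol through the ethics board.
3. Check every patient evaluated since April 2018 against the corrected criteria, and report any who would not have met them.
4. While editing, reconcile the two descriptions of who receives CT (Abstract against Stage 2), so that it is clear which patients are exposed.

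The cost is a one-line correction, or a short amendment, and a review of the records of patients evaluated so far; the article mentions at least 15 under follow-up. The design, the sample and the analysis need not change unless the check finds a patient enrolled outside the intended criteria.

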### Study Design

The study will be conducted in three steps including three patient visits. During visit 1 (day 1), sociodemographic information, modified Medical Research Council dyspnea questionnaire measures [37-39], the Saint Georges Respiratory questionnaire measures [40,41] for health-related quality of life, and most recent spirometry values will be recorded. In addition, all eligible patients will receive 40 mg/day oral prednisone for 7 days before endoscopy, to reduce pulmonary secretion and possible airways hyperreactivity. If the patient presents signs or symptoms that characterize an acute pulmonary infection, the inclusion will be postponed, and specific treatment will be prescribed to reschedule the inclusion.

During visit 2 (day 7 ± 3 days from visit 1), polysomnography and respiratory endoscopy will be performed. Full-night polysomnography will be performed in accordance with the recommendations of the American Academy of Sleep Medicine [42,43].

After polysomnography, a strap of 32 self-adhesive electrodes strap will be attached at the level of fourth intercostal space around the chest, and patients’ electrical impedance tomography data will be recorded concomitantly with bronchoscopy. Bronchoscopy will be performed in two stages: (1) sedation, analgesia, and evaluation of the presence of TBM followed by bronchial hygiene and (2) optimal pressure titrations to decrease airway collapse and EIT performance. The procedure sequence will be conducted in two stages, as described below.

#### Stage 1

The patient will be placed in a dorsal position for cardiac monitoring, noninvasive blood pressure measurement, and pulse oximetry. The nasal fossae will be lubricated with 2% topical lidocaine gel, followed by the introduction of nasopharyngeal catheter number 08 to provide supplemental oxygen. Fentanyl (0.5-2 μg/kg) and midazolam (0.03-0.05 μg/kg) will be administered intravenously to achieve light sedation. Propofol bolus (20-40 mg/dose) may be used to achieve the desired sedation. Next, the custom nasal mask of CPAP will be attached to the patient’s face, allowing the passage of the video-bronchoscope (Standard Q180 Olympus) with an external diameter of 4.9 mm and a working channel of 2.0 mm. Topical lidocaine at a dose of 1% without a vasoconstrictor (maximum dose of 7 mg/kg) will be instilled in the larynx and tracheobronchial tree. This will be followed by secretion aspiration. Subsequently, the presence of fixed or dynamic tracheal and bronchial collapse during the respiratory cycle will be analyzed and recorded. Direct observational assessment will be defined at the site with the greatest tracheal collapse and main bronchi during inspiratory and expiratory normal ventilation. Patients who do not present significant airway collapse will be excluded from the next step.

#### Stage 2

To evaluate the reduction of airway collapse, the bronchoscope will be fixed with the aid of a customized catheter in the tracheal region at least 2 cm before the area of the greatest collapse, previously defined by three bronchoscopists present in the examination room. The CPAP titration will start with a pressure of 0 cm H2O and be gradually increased in steps by 2 cm H2O every 10 complete respiratory cycles until a pressure of 18 cm H2O is reached (Figure 1).

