## Results

The project was submitted to the institutional review board on January 24, 2017, and approved on February 2, 2017 (Brazilian Research database number CAAE 64001317.4.000.0068). The project was registered in ClinicalTrails.gov (NCT03101059) on March 23, 2017. This protocol is a doctorate project. Patient evaluations started in April 2018. Planned recruitment is based on volunteers’ availability and clinical stability, and the interventions will be conducted at least once a month and completed at the end of 2020. A preliminary analysis of each case will be performed after each intervention, but detailed results are expected to be closed in the first quarter of 2021. We plan to publish 3 papers on this project. The proposed schedule for publication of the papers is as follows: the intervention protocol in 2019-2020; literature review about the concept of tracheobronchomalacia and airway collapse according to diverse uses ways to measure them and their definition in 2020; and results of the presence of tracheal collapse and the main bronchi of patients with MKS, through respiratory endoscopy and optimum positive pressure with CPAP that reduces or reverse it, in 2021.

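### The early edge of the visit 2 window, 4 days after visit 1, is too short for the 7-day prednisone course required before endoscopy, unless dosing starts before visit 1

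*Protocol article*

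**What the plan says.** Two adjacent paragraphs of the protocol article (Methods, Study Design) set the timing.

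- The visit 1 paragraph opens with "During visit 1 (day 1), sociodemographic information" and the other baseline records. It then adds that "all eligible patients will receive 40 mg/day oral prednisone for 7 days before endoscopy", to lessen secretions and any airway hyperreactivity.
- The following paragraph reads: "During visit 2 (day 7 ± 3 days from visit 1), polysomnography and respiratory endoscopy will be performed". Bronchoscopy comes after a full-night sleep study.

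The article gives no first-dose date. It does not mention dosing before visit 1, a shortened course, or closing the early part of the window until the course is complete.

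Three further statements bear on the consequences:

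- At Stage 1, once topical anaesthetic has been instilled, "This will be followed by secretion aspiration". Collapse is judged only after that.
- The Stage 1 result decides who goes on: "Patients who do not present significant airway collapse will be excluded from the next step".
- The software analysis in Stage 2 works by "comparing the area of collapse at 0 cm H2O pressure with the corresponding measurements at different applied pressures titrated during the procedure".

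**The concern.** The nominal interval between the visits equals the length of the steroid course. Any negative tolerance on that interval therefore cuts into the course, and a site can book visit 2 inside the permitted window and still miss the prednisone requirement.

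The protocol gives the steroid to bring airways to a prepared state before collapse is assessed. If some patients are examined after 4 doses and others after 7, that state may not be the same for everyone. The results exposed are those that compare or classify patients: whether collapse is present (one of the two main objectives), who enters titration, the comparison of patients with and without collapse, and the level of P1 and P2. The sample is small. The Statistical Analysis section reports at least 15 patients under follow-up, and with 15 enrolled one patient classified differently moves a proportion by 1/15, about 6.7 percentage points.

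**Working it through.** **Inputs (all from Study Design)**

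- Course: 7 days at 40 mg/day, so 7 × 40 = 280 mg.
- Gap *g* from visit 1 to visit 2: 7 - 3 = 4 to 7 + 3 = 10 days, which is seven permitted values.
- Order within visit 2: sleep study first, bronchoscopy afterwards. If bronchoscopy falls on the next morning, one more day is available.

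**Assumption:** the first dose is taken on the visit 1 day.

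**Base count.** Doses before the endoscopy day = min(*g*, 7). Two extras could add one dose each: counting a dose on the endoscopy day, and doing the endoscopy on the morning after the sleep study. Totals are capped at 7.

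| Gap *g* (days) | Doses, base count | mg | Shortfall | With one extra | With both extras |
|---|---|---|---|---|---|
| 4 | 4 | 160 | 3 doses, 120 mg | 5 | 6 |
| 5 | 5 | 200 | 2 doses, 80 mg | 6 | 7 |
| 6 | 6 | 240 | 1 dose, 40 mg | 7 | 7 |
| 7 to 10 | 7 | 280 | none | 7 | 7 |

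A 4-day gap never reaches 7 doses. A 5-day gap does so only with both extras, and a 6-day gap needs one of them. The remaining four of the seven permitted gaps have no conflict, because the course is tied to the endoscopy and can start later than visit 1.

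**Sensitivity to the day count.** If day 7 is a study-day number with visit 1 as day 1, the window runs from study day 4 to study day 10, so *g* = 3 to 9. The planned day itself then has *g* = 6, one dose short on the base count. Gaps of 3 and 4 days hold at most 3 + 2 = 5 and 4 + 2 = 6 doses, so both fail on every count. The table uses the reading more favourable to the protocol.

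**Check of the remedy.** With *g* restricted to 7 to 10 elapsed days, min(*g*, 7) = 7 on every permitted day, with no extras needed.

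**The case against.** The strongest reply is that the course is tied to the endoscopy and no start day is given, so prednisone might be prescribed before visit 1. Patients are already followed in the clinic, and the article does not tie consent or eligibility to visit 1. A site that wanted to obey both sentences could start early or simply book days 7 to 10. A first-dose date is also a detail that a condensed article may leave to the full protocol.

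Part of this stands: the conflict does depend on dosing no earlier than visit 1. But the instruction sits in the visit 1 paragraph, follows the baseline assessments, and precedes the rule that postpones inclusion for acute infection, so a visit 1 start is the natural reading. If sites are expected to avoid the early days, those days should not be in the window. The appeal to condensation does not help, because both conflicting figures are printed in the article.

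The second reply is that the consequence is unproven. Prednisone is preparation rather than the intervention, and no planned analysis uses it. Nothing in the document shows that 4 to 6 doses prepare the airway differently from 7. Secretions are aspirated before collapse is judged, and the exclusions in the Overview end with "acute cardiac arrhythmias, and refractory bronchospasm". Comparisons of collapse area and of impedance tomography across pressures are made within one patient in one session. This largely stands and limits the importance of the point. It does not remove it: only refractory bronchospasm is excluded, and classification at Stage 1 is a comparison between patients.

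**Conclusion.** The concern holds as a minor point. If prednisone starts no earlier than visit 1, the earliest permitted visit 2 cannot hold the required course on any count, and visits at 5 or 6 days hold it only with extra assumptions. On the base count the shortfall is 3, 2 or 1 doses (120, 80 or 40 mg of 280 mg).

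These figures describe dose, not bias. The size and direction of any effect on collapse status, entry to Stage 2, or P1 and P2 cannot be derived from the document, and neither can the frequency of early visits. The within-patient comparisons across pressures are not affected.

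**What to change.** In Study Design, set visit 2 at 7 to 10 days after visit 1 (7, +3/-0), in elapsed days, and state that the first prednisone dose is taken 7 days before the booked endoscopy. This makes the full course achievable on every permitted day.

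The alternative is to keep ±3 days and state that prednisone may start before visit 1. That also resolves the conflict, but it would start a systemic steroid ahead of the visit 1 assessments.

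According to the Results section, "Patient evaluations started in April 2018", so some patients will already have been through visit 2. For them, list the actual number of prednisone days descriptively where records allow.

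The cost is one sentence, the loss of three days of scheduling flexibility for visit 2, and a short look-back through existing records.
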